## Abstract

**Background:**

Antithrombotic treatment is a continuous therapy that is often performed in general practice and requires careful safety management. The aim of this study is to investigate whether a best-practice model that applies major elements of case management and patient education, can improve antithrombotic management in primary healthcare in terms of reducing major thromboembolic and bleeding events.

**Methods:**

This 24-month cluster-randomized trial will be performed with 690 adult patients from 46 practices. The trial intervention will be a complex intervention involving general practitioners, healthcare assistants, and patients with an indication for oral anticoagulation. To assess adherence to medication and symptoms in patients, as well as to detect complications early, healthcare assistants will be trained in case management and will use the Coagulation-Monitoring List (Co-MoL) to regularly monitor patients. Patients will receive information (leaflets and a video), treatment monitoring via the Co-MoL and be motivated to perform self-management. Patients in the control group will continue to receive treatment as usual from their general practitioners. The primary endpoint is the combined endpoint of all thromboembolic events requiring hospitalization and all major bleeding complications. Secondary endpoints are mortality, hospitalization, strokes, major bleeding and thromboembolic complications, severe treatment interactions, the number of adverse events, quality of anticoagulation, health-related quality of life, and costs. Further secondary objectives will be investigated to explain the mechanism by which the intervention is effective: patients’ assessment of chronic illness care, self-reported adherence to medication, general practitioners’ and healthcare assistants’ knowledge, and patients’ knowledge and satisfaction with shared decision making.

Practice recruitment is expected to take place between July and December 2012. Recruitment of eligible patients will start in July 2012. Assessment will occur at three time points: baseline and follow-up after 12 months and after 24 months.

**Discussion:**

The efficacy and effectiveness of individual elements of the intervention, such as antithrombotic interventions, self-management concepts in orally anticoagulated patients, and the methodological tool of case management, have already been extensively demonstrated. This project foresees the combination of several proven instruments, as a result of which we expect to profit from a reduction in the major complications associated with antithrombotic treatment.

**Trial registration:**

Current Controlled Trials ISRCTN41847489

## Background

Oral anticoagulation has been shown to be highly effective in preventing thromboembolic complications in patients for whom it is indicated [1,2]. Atrial fibrillation, the incidence of which increases with age and approaches 10% for individuals aged ≥80 years, carries the major risk of a stroke [3,4]. In Germany, large-scale epidemiological data are unavailable, hence it can only be estimated that about 1 million people are suffering from atrial fibrillation. The German Competence NETwork on Atrial Fibrillation (AFNET) has initiated a large nationwide patient registry to evaluate the current daily care of patients with atrial fibrillation in Germany [5]. The registry shows that anticoagulation for stroke prevention was given to 71% of patients considered eligible according to applicable guidelines and to 48.4% of low-risk patients, for whom guidelines do not recommend anticoagulation, meaning that overtreatment may also exist. In an international study that also included German patients, it was reported that only about 65% of patients requiring treatment and not presenting any contra-indications received anticoagulation treatment [6]. In addition, due to relatively narrow therapeutic ranges, it is often only a small percentage of international normalized ratio (INR) values that are found to be within the target range. This proportion, as German studies of patients receiving routine care have shown, can be as low as <40% of INR measurements [7,8]. As it is well known that about 44% of bleedings occur when INRs are above the therapeutic range, that about 50% of thromboembolic events happen when INR values are too low [9], and that improved oral anticoagulation is an indirect parameter for the reduced incidence of thromboembolic and hemorrhagic events, there is a real need to improve anticoagulation control. Furthermore, our own analysis of the oral anticoagulation therapy treatment process in 16 general practices in Germany identified safety gaps. These were mainly found in documentation, patient participation, knowledge of side effects, and interactions [10].

The new oral agents dabigatran, a direct thrombin inhibitor, and rivaroxaban, a direct Factor Xa inhibitor, have recently been approved for patients with a long-term indication for antithrombotic treatment. Dabigatran has been approved for patients with nonvalvular atrial fibrillation and one additional risk factor for stroke, with approval primarily based on the results of the RE-LY study [11]. Compared to warfarin, dabigatran administered at a dose of 150 mg was associated with lower rates of stroke and systemic embolism but similar rates of major bleedings. However, in November, the European Medicines Agency (EMA) updated the safety label for dabigatran after reports of several cases of fatal bleeding events in patients of relatively high age that had renal insufficiency and low body weight [12]. Rivaroxaban was approved in December 2011 for two long-term indications (patients with nonvalvular atrial fibrillation and one additional risk factor for stroke and to prevent the reoccurrence of deep venous thrombosis and pulmonary embolism). With regard to atrial fibrilliation, data primarily based on the ROCKET-AF study could not show superiority versus warfarin in terms of a reduction in the incidence of strokes, systemic embolisms, or major bleeding complications [13]. However, as both new oral agents have recently been approved, special caution relating to drug interactions, renal insufficiency, and low body weight (as with dabigatran) is required because unknown risks may exist in an unselected patient population [14].

The efficacy and effectiveness of antithrombotic treatment have already been extensively demonstrated. However, no study has yet analyzed a complex intervention that incorporates further elements of proven benefit, such as self-management of OAC patients and case management in general practices. Systematic reviews [15-17] and a randomized controlled trial (RCT) in elderly patients [18] have confirmed that thromboembolic events and deaths can be reduced in patients performing self-management, with no difference in the incidence of major hemorrhagic complications. In the long-term RCT of elderly patients, self-management of OAC was able to improve general treatment satisfaction, as well as having a positive effect on treatment-related quality of life [19]. Case management is generally defined as a clinical, educative, and social service provided to individuals with high needs [20]. It mostly includes planned services for coordinating care, systematic follow-up, and evidence-based guidelines. Beneficial effects of case management in primary care have been shown—partially based on our own results—for many chronic diseases (*e.g.*, diabetes [21], depression [22,23], chronic heart failure, osteoarthritis [24] and other diseases, as well as continuous therapies [25]). As it is proactive and patient oriented, case management can be expected to increase adherence to antithrombotic therapy and, therefore, improve quality of care.

The aim of this study is, therefore, to improve antithrombotic management in primary healthcare by applying major elements of case management, including patient education, and to test their effectiveness in terms of reducing major thromboembolic and bleeding events.

## Methods/design

### Study design

Primary care management for optimized antithrombotic treatment (PICANT) is to be a cluster RCT with the general practice as the unit of randomization (see Figure 1). Since healthcare assistants (HCAs) and general practitioners (GPs) trained in the intervention will not be in a position to provide care as usual, a clustered design (with practices as clusters of 15 patients per practice) was chosen in order to reduce treatment group contamination. Practices will be randomly allocated to the case management or usual care arm in a ratio of 1:1. Practice allocation to treatment groups will be performed using the web-based randomization tool “Randomizer for Clinical Trials,” developed by the Institute for Medical Informatics, Statistics and Documentation, Medical University of Graz (http://www.randomizer.at). After patient recruitment and baseline assessment have been completed in a practice, a member of the Institute of General Practice will use the web-based randomization tool to obtain information on the allocated treatment group. Allocation concealment will take place after completion of the baseline documentation for all study patients from a specific practice, but before the intervention begins.

**Figure 1 F1:**
[figure not shown]
Description of schedule and expected duration of the PICANT trial.

### Practice and patient recruitment

The trial will be primarily conducted in general practices in the state of Hesse, Germany.

Practices are eligible for the trial if they provide health services to persons with German statutory health insurance and have a software system at their disposal that is capable of detecting potentially eligible patients.

Practices already participating in studies aimed at improving quality of oral anticoagulation will be excluded. Participating GPs must sign an informed consent form and agree to implement the study protocol. Potentially eligible practices will be identified by means of an address database provided by the Association of Statutory Health Insurance Physicians of Hesse. The practices will be stratified according to the number of inhabitants of the postal area in which the practice is located. Based on our own recruitment experience during previous studies involving general practices in Hesse [26], we would expect to have to contact >500 practices to recruit the required number of practices for the trial. In a first step, we will write a formal letter inviting approximately 500 randomly selected practices to participate in the study. If the required number of participating practices is not achieved, further randomly selected practices (in steps of 250 practices at a time) will be contacted and asked to participate. The random samples will be selected by means of the random number generator function in Microsoft Excel® (Microsoft Corporation, Redmond, WA, USA). The random selection of practices will be performed by a member of the study team in the presence of a third person who is not involved in the study.

Each participating practice will be asked to create a screening list of potentially eligible patients by means of their software and on the basis of predefined instructions. At the first practice visit, the GP will go through the screening list in the presence of a member of the study team and assess the inclusion and exclusion criteria of the patients until 30 eligible patients have been identified. To avoid a selection bias, the order of the patients assessed for eligibility will be randomly chosen by means of the random number generator function in Microsoft Excel. The 30 eligible patients will then receive a written invitation from the GP to participate in the study. Once 15 patients have been included, patient recruitment will be ceased. This recruitment strategy was developed in accordance with previous studies [26,27]. The process used to identify eligible study patients was pilot tested in seven practices and found to be feasible.

### Inclusion and exclusion criteria for patients

Adult patients of ≥18 years of age and with a long-term indication for oral anticoagulation (atrial fibrillation/ flutter, recurrent venous thromboembolism or pulmonary embolism, mechanical heart prosthesis, and others, such as hereditary coagulopathy, intracardial thrombosis) and an indication for coumarins, antiplatelet therapies, or the new antithrombotic agents rivaroxaban and dabigatran will be included in the study. They should regularly attend the GP’s practice and must sign an informed consent form. Exclusion criteria for patients are dementia, diseases resulting in a life expectancy of less than six months, psychosis, severe sight disorders or auditory defects, alcohol or drug abuse, residence in institutions (*e.g.*, nursing homes or residential care homes) that do not allow study participation, and a lack of German language skills.

### Outcome measures

The primary patient-relevant endpoint of the trial is the combined endpoint of all thromboembolic events requiring hospitalization and all major bleeding complications, as assessed by the GP and documented in the case report form. Major bleeds include (1) fatal bleeding; (2) symptomatic bleeding in a critical area or organ, such as intracranial, intraspinal, intraocular, retroperitoneal, intraarticular or pericardial, or intramuscular with compartment syndrome; and/or (3) bleeding causing a fall in the hemoglobin level of 20 g/L (1.24 mmol L-1) or more or leading to the transfusion of two units of packed red blood cells [28]. Thromboembolic events requiring hospitalization include arterial embolism (stroke, transient ischemic attack, myocardial infarction, peripheral arterial embolism), venous thromboembolism (*e.g.*, deep venous thrombosis, pulmonary embolism), and valve thrombosis [18,29].

The following key secondary endpoint(s) will be evaluated by means of the case report forms (filled in by the GPs) and patient questionnaires: all-cause and cause-related mortality rates, frequency and duration of hospitalization, number of recurrent strokes (ischemic and hemorrhagic stroke), major bleeding and thromboembolic complications (as defined for the primary endpoint), the number of patients with at least one potentially severe treatment interaction, total number of potentially severe treatment interactions involving oral anticoagulants, the number of adverse events, quality of anticoagulation (*e.g.*, time within therapeutic range) [30], health-related quality of life (EQ-5D) [31], and costs.

Further secondary objectives will be investigated to explain the mechanism by which the intervention is effective: patients’ assessment of chronic illness care (PACIC) [32], self-reported adherence to medication (Morisky Questionnaire) [33], general practitioners’ and healthcare assistants’ knowledge (self-developed knowledge questionnaire), patients’ knowledge (questionnaire developed by Hua) [34], and satisfaction with shared decision making (Man-Song Hing test) [35].

All primary and secondary outcomes will be measured at patient level at baseline (T0) and at follow-ups at 12 months after baseline (T1) and 24 months after baseline (T2). All events will be documented in case report forms and cross-checked by reviewing doctors’ reports, discharge letters, and death certificates. Allocation concealment will take place after completion of the baseline documentation for all study patients from a specific practice, but before the intervention begins.We will conduct qualitative interviews with patients, HCAs, and GPs to evaluate the perceptions of and satisfaction with practice-based case management and to study the general practitioners’ reasons for changing medication to the new antithrombotic drugs (dabigatran or rivaroxaban).

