### Intervention group

Practices randomized to the intervention group will receive a complex intervention, including the provision of additional tools and guidelines to GPs and their practice teams. The HCAs will be trained in performing case management and educating patients (including a patient information leaflet and a video developed by Hua *et al.*) [34]. To assess adherence to medication and symptoms in patients, as well as detect complications early, HCAs will be trained in case management and will regularly monitor patients by means of the Coagulation-Monitoring List (Co-MoL). Practice routines will be improved. In addition, the GPs will be contacted immediately after randomization and provided with further explanations of case management by telephone. Quality circles will be held three times during the course of the trial (shortly after baseline assessment and after 12 and 24 months) to discuss the practical problems of anticoagulation and individual case reports.

For patients, the intervention will include information (patient information leaflet and a video developed by Hua *et al.*[34]), treatment monitoring via the Co-MoL, and encouragement to participate in a self-management course where they will learn how to carry out self-testing and self-dosing.

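### The primary endpoint counts fatal bleeding unconditionally but has no fatal category for thromboembolism, so a non-hemorrhagic thromboembolic death without admission is uncounted or left to the GP's judgement

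*Protocol article*

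**What the plan says.** The protocol article, Outcome measures, defines the primary endpoint as the "combined endpoint of all thromboembolic events requiring hospitalization and all major bleeding complications, as assessed by the GP".

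- **Thromboembolic half:** "Thromboembolic events requiring hospitalization include arterial embolism (stroke, transient ischemic attack, myocardial infarction, peripheral arterial embolism"), then "venous thromboembolism (*e.g.*, deep venous thrombosis, pulmonary embolism), and valve thrombosis". The admission condition governs the whole list, and no fatal category is named.
- **Bleeding half:** "Major bleeds include (1) fatal bleeding; (2) symptomatic bleeding in a critical area or organ", and so on. Fatal bleeding comes first and carries no admission condition.
- **Secondary endpoints:** "all-cause and cause-related mortality rates, frequency and duration of hospitalization" are included. The secondary thromboembolic endpoint takes over the primary definition.
- **Event checking:** doctors' reports are reviewed, together with "discharge letters, and death certificates".

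The abstract and the section Sample size calculation repeat the admission condition. The section Intervention group gives the purpose of the healthcare assistants' monitoring: "To assess adherence to medication and symptoms in patients, as well as detect complications early". The section Statistical hypotheses, methods, and analyses specifies the first event per patient and a Cox model extended for clustering.

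**The concern.** The two halves of the composite treat death differently. A patient who dies at home of a pulmonary embolism has had a worse outcome than one admitted with a transient ischemic attack, yet on a literal reading only the second has a primary event. The stated aim is to reduce major thromboembolic and bleeding events, and a fatal thromboembolism belongs among them.

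The omission need not be the same in both arms. Closer monitoring could plausibly turn a death at home (not counted) into an admission (counted), so that a better course is scored as an event. A thromboembolic death without admission that the intervention prevents earns no credit. The documents say nothing about how often either would happen.

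**Working it through.** **Reading the definition**

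| Outcome | Counted as a primary event? |
|---|---|
| Fatal bleeding, wherever it occurs | Yes |
| Fatal hemorrhagic stroke without admission | Yes, as fatal or intracranial bleeding |
| Thromboembolic event with admission, fatal or not | Yes |
| Transient ischemic attack with admission | Yes |
| Fatal ischemic stroke, infarction, pulmonary embolism or valve thrombosis without admission | Literally no; yes if *requiring* is taken to mean *would have required* |

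Only the last row is in dispute, and no other section of the article resolves it.

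**Reproducing the planned size**

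Inputs from Sample size calculation: p1 = 0.15; p2 = 0.075 (50% reduction); two-sided 5%; power 80%; ICC 0.01. Study design gives 15 patients per practice.

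With p̄ = (p1 + p2)/2,

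n = [1.960·√(2p̄(1−p̄)) + 0.842·√(p1(1−p1) + p2(1−p2))]² / (p1−p2)²

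- With p̄ = 0.1125, n = 277.5, rounded up to 278, as stated.
- Design effect = 1 + 14 × 0.01 = 1.14, and 278 × 1.14 = 316.9, so 317, as stated.
- 23 practices × 15 = 345, as stated.
- Expected events at 317 per group: 317 × 0.15 = 47.6 and 317 × 0.075 = 23.8.
- Effective size for power: 317/1.14 = 278.1 per group.

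Power = Φ{[(p1−p2)·√278.1 − 1.960·√(2p̄(1−p̄))] / √(p1(1−p1) + p2(1−p2))} = 80.1% at the planning rates.

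**Case A (assumption): the planning rates already include these deaths, and the same share of all events goes uncounted in both arms**

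| Share uncounted | Rates | Control events lost (of 47.6) | Power |
|---|---|---|---|
| 2.5% | 14.6% vs 7.3% | 1.2 | 79.0% |
| 5% | 14.25% vs 7.125% | 2.4 | 77.8% |
| 10% | 13.5% vs 6.75% | 4.8 | 75.3% |

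If half of all events are thromboembolic, 2.5% to 10% of all events means that 5% to 20% of thromboembolic events are fatal without admission. Neither share comes from the documents.

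**Case B (assumption): the planning rates describe the endpoint as worded, and these deaths come on top**

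Power once they are counted:

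| Control rate of such deaths | Intervention halves them | Intervention has no effect on them |
|---|---|---|
| 0.5% | 15.5% vs 7.75%: 81.5% | 15.5% vs 8.0%: 78.6% |
| 1% | 16.0% vs 8.0%: 82.9% | 16.0% vs 8.5%: 77.1% |
| 2% | 17.0% vs 8.5%: 85.4% | 17.0% vs 9.5%: 74.3% |

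Power can therefore move either way. These figures follow the plan's own two-proportion calculation and do not model the Cox analysis or any difference between arms in what goes uncounted.

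**The case against.** The strongest reply is that the exclusion is inferred. The text speaks of events that require admission, not events that led to one, and a lethal stroke could be said to meet that threshold. Death certificates are among the sources checked, so deaths fall within event ascertainment. This stands as far as certainty goes: the article does not say outright that such deaths are excluded. It does not remove the problem. The certificates also serve fatal bleeding and mortality, and the looser reading leaves the most severe events to a GP whose practice was randomized and who, in the intervention arm, is telephoned about case management straight after randomization.

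It can also be said that the article is condensed and that coding rules may lie in documents not shown. That is fair for the handling of deaths in the Cox model. A reader might infer that these patients are censored at death, and that this is informative censoring. The article does not say so; it follows only as a likely consequence of a first-event analysis. The endpoint definition is a different matter, because it is written out here and is explicit about death for bleeding.

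Tying the component to admission has a real merit: a discharge letter supports the diagnosis, whereas the cause of an unattended home death is a judgement. Cause-related mortality is also reported as a secondary endpoint, so a marked imbalance could be seen. Both points lower the severity, but neither repairs the primary comparison.

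**Conclusion.** The point holds in a limited form. The definition counts fatal bleeding without condition and gives fatal thromboembolism no place of its own. Non-hemorrhagic thromboembolic deaths without admission are then either outside the primary endpoint or dependent on an unblinded GP's reading of one word. The same gap passes to the secondary thromboembolic endpoint.

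Three stronger readings are tempting and not supported:

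- **That every fatal stroke outside hospital is missed.** Hemorrhagic strokes count as bleeding.
- **That the intervention gets no credit for preventing fatal events.** Credit is lost only for thromboembolic deaths without admission.
- **That the trial demonstrably loses power.** Under the assumed ranges, power is about 79% to 75% if the planning rates include these deaths and they go uncounted. If the deaths come on top of the planning rates, counting them gives about 82% to 85% when the intervention halves them, or 79% to 74% when it does not affect them.

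The documents give no rate for these deaths and no figure for a difference between arms, so the size of any bias cannot be stated. The case for change is the validity of the endpoint, not power. Severity is moderate.

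**What to change.** Define the component as *thromboembolic events that are fatal or require hospitalization*, both in the primary endpoint and in the secondary endpoint that borrows its definition. Settle this before outcome data are reviewed. Classify deaths without admission from the death certificates and doctors' reports that are already reviewed.

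The cost is one phrase in the definition and the matching entry in the case report form, with no new data source. The drawback is that the cause of some home deaths will be uncertain. A prespecified sensitivity analysis that leaves out thromboembolic deaths without admission would show whether the result depends on them.

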### Sample size calculation

Sample size was calculated by using the primary combined endpoint of all thromboembolic events requiring hospitalization and all major bleeding complications in the 24-month intervention period.

Based on data from previously published studies [11,18,38], we anticipate an event rate of 15% over the 24-month period in the routine-care group. A 50% reduction in thromboembolic events and major bleedings is expected in the case-management group. To detect a 50% reduction between the two treatment groups using a chi-square test with a two-sided significance level of 5% and a power of 80%, a sample size of 278 patients per group is needed. To account for the design effect in this cluster RCT, the sample size will have to be inflated by the design effect (DE), where DE = 1 + (*m* − 1) ICC (*m* is the average cluster size and ICC is the intraclass correlation coefficient). In accordance with Campbell *et al.*, 2007, and Campbell 2000 we will use an estimate of 0.01 for the ICC [39,40]. On the assumption that it will be possible to identify about 30 eligible patients in each general practice and that 50% of these can be recruited for the study, the adjusted sample size per group is 317. To account for drop outs and incomplete follow-up, our objective is to include 345 patients (23 general practices) per group. In addition, we will include a further four practices in each group in order to be prepared for any practice loss. The sample size calculation was performed using nQuery Advisor 7.0 (Statistical Solutions Ltd., Cork, Ireland).

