### Timeframe of the study

Practice recruitment is expected to take place between July 2012 and December 2012 (see Figure 1). Recruitment of eligible patients and baseline data collection will start in July 2012. After cluster randomization, teams in intervention practices will be consecutively trained between August and December 2012, prior to the beginning of the intervention. Data collection for the 12-month assessment is scheduled from June 2013 to January 2014 and from June 2014 to January 2015 for the 24-month assessment.

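### Follow-up runs 24 months from a baseline that precedes randomization and training, so intervention patients get less than the 24-month intervention period assumed in the sample size

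*Protocol article*

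**What the plan says.** All statements are in the protocol article.

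- **Visit clock (Outcome measures).** Outcomes are measured at baseline (T0) and "at follow-ups at 12 months after baseline (T1) and 24 months after baseline (T2").
- **Order of steps (Study design).** The allocation is looked up in the web tool "After patient recruitment and baseline assessment have been completed in a practice". The intervention begins only after this.
- **Training (Timeframe of the study).** Baseline data collection starts in July 2012. After randomization, "teams in intervention practices will be consecutively trained between August and December 2012, prior to the beginning of the intervention".
- **Sample size (Sample size calculation).** The endpoint is counted as thromboembolic events requiring hospitalization plus "major bleeding complications in the 24-month intervention period". For the control rate, "we anticipate an event rate of 15% over the 24-month period in the routine-care group". For the effect, "A 50% reduction in thromboembolic events and major bleedings is expected in the case-management group".
- **Analysis (Statistical hypotheses, methods, and analyses).** Each patient's first event is used, in a Cox model extended for clustering. The origin of the time axis is not given.

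No section restarts the clock at randomization, training or first case-management contact, and the sample size makes no allowance for a lag.

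**The concern.** Three statements cannot all hold: T2 is 24 months after baseline, the intervention starts some time after baseline, and the sample size counts events over a 24-month intervention period. Time under intervention at T2 is 24 months minus the lag, and the sequence of steps makes the lag greater than zero for every intervention patient. Within a practice it is longest for those enrolled first, who wait until recruitment there is complete (up to 15 patients).

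Two things are at stake. First, time at the start of follow-up that the intervention cannot influence pulls the estimated effect towards no difference and lowers power. Second, if analysis time starts at T0, the first-event rule means that an event before allocation becomes the patient's outcome, and anything that happens to that patient under the intervention is ignored. Such events carry no information about the intervention.

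**Working it through.** **Inputs.** Control risk is 15% over 24 months and the reduction 50%, so 7.5% under intervention. The calculation was made "using a chi-square test with a two-sided significance level of 5% and a power of 80" per cent. The ICC is 0.01 and the recruitment target 345 per group (all from Sample size calculation). The cluster size is 15 (Study design).

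**The plan's own figures.** With mean risk (0.15 + 0.075)/2 = 0.1125:

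n = [1.96 √(2 × 0.1125 × 0.8875) + 0.8416 √(0.15 × 0.85 + 0.075 × 0.925)]² / 0.075² = 277.5, so 278 per group, as stated.

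Design effect = 1 + 14 × 0.01 = 1.14. Then 278 × 1.14 = 316.9, so 317, as stated. 23 × 15 = 345, as stated. The arithmetic is sound. It assumes the full 50% reduction over the whole 24 months.

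**Model for the lag.** Let L be the months from a patient's baseline to the start of the intervention. L is not in the document, so it is an assumption shown as a range. Assume constant hazards and no effect during L:

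- control hazard = −ln(0.85)/24 = 0.00677 per month
- intervention hazard = −ln(0.925)/24 = 0.00325 per month (hazard ratio 0.48)
- intervention-arm risk at month 24 = 1 − exp[−0.00677 L − 0.00325 (24 − L)]

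Power = Φ{[(p₁ − p₂)√n − 1.96 √(2p̄(1 − p̄))] / √(p₁(1 − p₁) + p₂(1 − p₂))}, with p₁ = 0.15. It is computed at n = 278 (the effective size after the planned losses) and at n = 345/1.14 = 302.6 (nobody lost).

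Example, L = 1: p₂ = 0.0783, difference 0.0717, p̄ = 0.1141. Power at 278 = Φ[(1.196 − 0.881)/0.447] = Φ(0.705) = 76.0%.

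| L (months) | Risk, intervention arm | Reduction over 24 months | Power, effective 278 | Power, all 345 followed | n per group for 80% (after design effect) |
|---|---|---|---|---|---|
| 0 | 7.50% | 50.0% | 80.1% | 83.3% | 278 (317) |
| 0.5 | 7.66% | 48.9% | 78.1% | 81.4% | 292 (333) |
| 1 | 7.83% | 47.8% | 76.0% | 79.4% | 308 (352) |
| 2 | 8.15% | 45.7% | 71.5% | 75.1% | 342 (390) |
| 3 | 8.47% | 43.5% | 66.8% | 70.5% | 381 (435) |

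A straight-line mixture of the two risks, 15% × L/24 + 7.5% × (24 − L)/24, gives nearly the same: 76.1%, 71.8% and 67.3% at 278 for L = 1, 2 and 3.

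**Moving only the start of analysis time.** Suppose events count from the start of the intervention but T2 stays 24 months after baseline. Follow-up is then 24 − L months in both arms. For L = 1, 2 and 3, power at 278 is 78.5%, 76.7% and 74.9%. The dilution is gone but events are lost, which is why the visits should move too.

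**What starting at randomization leaves.** Split L into A (baseline to randomization) and B (randomization to start of the intervention). With time zero and T2 both set from randomization, A drops out and the control risk is again taken over a full 24 months. B remains, so the table is then read at B instead of A + B.

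**The case against.** The strongest reply is that the text on outcome measures says when outcomes are measured, not from when events count in the Cox model. Time zero is the kind of detail an SAP settles, and the SAP is announced but not shown. The schedule figure is also not available here. This much stands: a reader might infer that pre-allocation events will be counted, but the document does not say so, and that part of the point is conditional. The mismatch over exposure is not conditional, because the protocol itself fixes the visit dates, the order of steps and the period behind the sample size. An SAP cannot lengthen follow-up once the visits have been held.

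Second, the lag may be short. Practices are randomized one by one, need only 15 patients each, and are trained consecutively. GPs are telephoned straight after randomization, and the first quality circle comes soon after baseline. This stands as a limit on size. A reader might combine a July 2012 baseline with December 2012 training to get a five-month lag and power of about 57% at 278. That is a calendar extreme, and nothing in the text shows that any practice would wait so long.

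Third, the timetable states: "Data collection for the 12-month assessment is scheduled from June 2013 to January 2014 and from June 2014 to January 2015 for the 24-month assessment". A reader might take the June openings as an error, since no patient reaches 12 months before July 2013. The documents do not support this. Recruitment runs from July to December 2012, and each window opens one month before and closes one month after the matching anniversaries, which fits a one-month visit tolerance.

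Fourth, the 50% is a planning expectation and could be read as the net effect over follow-up. That is possible, but the sample size text ties the events to the intervention period.

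Finally, collecting baseline before allocation protects a cluster trial against selective recruitment and should stay. The dilution is conservative and does not raise the type I error.

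**Conclusion.** The point holds as a contradiction between the visit clock and the sample size period. By the protocol's own sequence, intervention patients have less than 24 months under intervention at T2, while the 50% reduction and 80% power assume the full period. Pre-allocation events would enter as outcomes only if analysis time starts at baseline, which is left open.

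The size depends on a lag that the document does not give. With constant hazards and no effect before the intervention starts, power at an effective 278 falls by about 2 percentage points for half a month, 4 for one month, 9 for two and 13 for three. The 15% control risk is unaffected, and the stated 278, 317 and 345 are correct for their inputs. This does not invalidate the trial. It is an avoidable loss of power and an inconsistency that should be resolved.

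**What to change.** 1. State that time in the primary Cox analysis starts at the practice's randomization date in both arms, and treat events between a patient's baseline and that date as baseline history.
2. Time T1 and T2 at 12 and 24 months after that date, and align the data-collection windows. Keep baseline before randomization.
3. Allow in the assumed effect for the wait from randomization to training. It is the same for no two practices, belongs in the intention-to-treat effect, and is not removed by step 1. State the expected length and read power at that lag.
4. If the visits cannot move, describe the period as 24 months of follow-up from baseline instead of a 24-month intervention period, and restate the expected reduction and power for the shorter exposure.

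Cost: a few sentences on time zero and visit timing. Each practice's visits shift by its baseline-to-randomization interval, so the last data collection may end slightly later. The January 2015 closing date already covers 24 months from a December 2012 randomization, so the extension should be small.
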